#### (ii) Walking programme (WP)

Within one week of randomisation, participants will commence the WP, the focus being to increase physical activity through a graded walking programme. The WP is based on previous effective programmes in healthy sedentary adults [29,30,57,58] as no previous programmes for LBP are available.

As with the SEC, each participant will attend the physiotherapy department for an initial individual assessment, where there will be discussion and agreement between the therapist and the patient on short and long-term goals; recording of the patient's exercise capabilities and perceived barriers to recovery and the individual's treatment expectations. The therapist will use the information recorded in the exercise diary to inform the starting point for the eight week progressive WP; the minimum being a 10 minute walk (approx 1200 steps) on at least four days per week to be decided with, where possible, one day's rest between walks. The aim of the programme is to progress to the American College of Sports Medicine guidelines of 30 minutes moderate intensity walking on five days per week by week five [20], and then to maintain this level for the remainder of the programme. The 30 minutes brisk walking may be accumulated in two or three shorter bouts if this is more attainable e.g. three 10 minute walks [30,58]. A recent review found no difference in the positive effects on cardiovascular fitness of empirical studies of accumulated or continuous physical activity in sedentary adults and highlighted the need for research to evaluate if accumulated exercise may increase compliance in previously sedentary adults [59]. All participants will be encouraged to use the Borg Breathlessness scale to establish their walking speed: targeting level three (moderate breathlessness) to four (somewhat severe), the minimum level required to achieve the benefits related to exercise [55,56].

Participants will be contacted once per week by telephone by the Chartered Physiotherapist who performed the initial assessment to progress their walking frequency and duration based on their exercise diary record of the previous week's walking, and to provide encouragement. These telephone calls will be based around a specifically developed telephone script based upon CBT principles. Participants will be advised that just like athletes, any unaccustomed exercise is likely to produce some muscle soreness [8]. Participants will use their Yamax Digiwalker Pedometer [60] as a motivational feedback tool, providing immediate information on activity levels [61].

Adherence with the walking programme will be assessed by the frequency, distance, number of steps taken and duration of walks recorded in the exercise diary. Specific adherence levels will be established once the trial is complete. At the end of the intervention subjects will reattend the physiotherapy department for a review appointment with a view to discharge from physiotherapy.

#### (iii) Usual Physiotherapy (UP) -Control Group

Within one week of randomization, participants will commence individual usual physiotherapy at the discretion of the treating physiotherapist in the participating hospital. All physiotherapy treatments and the number of visits will be recorded for the study period in previously designed treatment record forms. On the basis of a previous RCT by the Principal Investigator in the Republic of Ireland public physiotherapy health service the anticipated mean (SD) number of treatments is 5.8 over a mean (SD) of 7.7 weeks (5.8) weeks [54]. A multimodal approach of education/advice, manipulative therapy and exercise therapy will be permitted on the basis of the results of previous surveys of physiotherapy practice in the UK and Ireland [32-34]. As part of this it is expected that subjects will be provided with an individualized exercise programme at the discretion of the treating therapist but will not be permitted to attend group exercise class or undertake a walking programme during the trial. Adherence will be assessed by the number of visits prior to discharge from physiotherapy.

### Adverse effects or events

No adverse events, apart from minor musculoskeletal complaints in the WP group, are anticipated but will be documented by type, length of time, and frequency should they occur [62].

### Data Analysis

Analysis will be by intention to treat. All participants and group allocation will be coded, sociodemographic data coded, and outcome questionnaires scored, and all data entered into the Statistical Package for the Social Sciences database for analysis following data cleaning and checking for errors. Analysis of the clinical outcome data will be performed by the statistician who will remain blinded to group identification until analysis is complete. Between group analyses will be performed to test for between group differences in each outcome from baseline at follow-up. Continuous outcome variables will be analysed using a mixed between-within repeated measures analysis of variance if the assumptions for parametric statistics hold. If substantial evidence of non-normality is found appropriate alternative (non-parametric) tests will be applied, and specified as the primary analysis method.

Using data from the cost diaries, the extent to which each of the interventions has impacted on subsequent use of health care will also be calculated and will cover all identifiable health care costs. The direct and indirect costs to patients receiving each intervention will be obtained. The health care services costs incurred during the intervention and year to follow up will be calculated using the relevant observable prices. Where prices cannot be observed shadow prices will estimated; mean and median health care utilization rates and associated direct service costs in addition to indirect and direct patient costs will be calculated for both intervention groups. Relationships between presenting LBP severity and utilization/cost will be investigated. An additional cost effectiveness analysis will use the magnitude of a mean and median change on the Oswestry Disability Questionnaire as the natural unit of outcome.

The resulting scores from the EQ-5D health state and the visual analog scale will be used to generate the health state utility values necessary for the within trial cost utility analysis (CUA). The CUA will allow the outcomes of this study to be compared to other studies allowing the relevant short term benefit of the interventions to be assessed.

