### Quantitative study

#### Design

The study will be a prospective randomized controlled trial (RCT) with three arms (i) walking programme, (ii) a supervised exercise class, (iii) usual physiotherapy of up to 8 weeks duration. Outcomes will be assessed at baseline and 3, 6 and 12 months [follow-up by pre-paid postage].

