### Sample Size

A total of 189 patients (n = 63 per group) will be required for 80% power to detect a 4 point difference between groups on the primary outcome, the Oswestry Disability Index [39], with 95% confidence using a two-tail between-within repeated measures ANOVA test of difference between group means. Based on the results of previous LBP trials investigating exercise [11] and using postal follow-ups [40], we anticipate a 30% loss to follow-up. Thus we aim to recruit 82 subjects per group (total 246 subjects).

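### Unless data are imputed first, the repeated-measures ANOVA named for the primary outcome drops patients with an incomplete set of ODI scores, which sits badly with the intention-to-treat commitment

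*Protocol article*

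**What the plan says.** All references are to the protocol article.

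- **Method.** Data Analysis: "Continuous outcome variables will be analysed using a mixed between-within repeated measures analysis of variance if the assumptions for parametric statistics hold". Sample Size names the same test for the ODI; the calculation is made "with 95% confidence using a two-tail between-within repeated measures ANOVA test of difference between group means".
- **Population.** Data Analysis: "Analysis will be by intention to treat". No qualification follows.
- **Software.** Data Analysis has "all data entered into the Statistical Package for the Social Sciences database for analysis following data cleaning and checking for errors".
- **Visits.** Design: "Outcomes will be assessed at baseline and 3, 6 and 12 months [follow-up by pre-paid postage". The primary objective, at the end of Background, is the between-group contrast in ODI change at 6 months.
- **Loss.** Sample Size: "we anticipate a 30% loss to follow-up". The visit to which this applies is not given. The base requirement is 63 per group (189), and recruitment is raised to allow for loss: "Thus we aim to recruit 82 subjects per group (total 246 subjects").

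**The concern.** In this method, mixed means one between-patient factor (group) and one within-patient factor (time). It is not a likelihood-based mixed-effects model. The classical between-within ANOVA works on complete rows. If a score is missing at any visit entered, the patient leaves the whole test, and the SPSS repeated-measures procedure behaves in this way.

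Two things are at stake. First, a patient with baseline and 6-month ODI but no 3-month or 12-month form would be lost from the primary analysis although the primary outcome was observed. Second, those who return every form are a selected subset of the randomised groups. The arms differ in contact (a weekly class, weekly telephone calls, usual physiotherapy at the therapist's discretion) and patients are not blinded, so loss that differs by arm and is related to outcome is plausible. An unqualified intention-to-treat commitment is meant to guard against that kind of comparison.

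**Working it through.** **Step 1. The plan's own sample size.** Inputs from Sample Size: difference 4 ODI points, power 80%, two-sided 5%, 63 per group. No SD is given, so it must be assumed.

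n per group = 2 × SD² × (1.960 + 0.842)² / 4²

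With SD 8 this is 2 × 64 × 7.85 / 16 = 62.8, so 63. (SD 7 gives 49, SD 9 gives 80, SD 10 gives 99.) The 63 is thus consistent with a pairwise comparison at an SD of about 8. Recruitment of 246 matches 189 × 1.3 = 245.7. Loss is added on top of the number the ANOVA needs, so the article itself treats lost patients as not contributing to the primary test.

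**Step 2. Who stays in the ANOVA.** Assume that all 246 have a baseline score, that baseline and all three follow-ups enter the model, and that nothing is imputed. Let p be the chance of missing a form, independently at each follow-up.

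- With a 6-month score: 246 × (1 − p)
- With all forms: 246 × (1 − p)³
- Observed 6-month scores discarded: the difference

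For p = 0.10: 246 × 0.9 = 221.4; 246 × 0.729 = 179.3; difference 42.1.

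Here 1 − 0.729 = 27% of patients miss at least one form, which is close to the 30% that the article expects overall.

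**Step 3. Dependence on the pattern of loss.** All patterns below are assumptions; the article gives none.

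| Assumed pattern | 6-month ODI observed | All forms | 6-month scores discarded |
|---|---|---|---|
| All 30% leave for good before 3 months | 172 | 172 | 0 |
| Permanent loss reaching 10%, 20%, 30% at 3, 6, 12 months | 197 | 172 | 25 |
| Independent, 10% per form | 221 | 179 | 42 |
| Independent, 20% per form | 197 | 126 | 71 |

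Source of the counts: 246 × 0.7 = 172.2; 246 × 0.8 = 196.8; 246 × 0.8³ = 126.0. In the last row 1 − 0.512 = 49% miss at least one form, more than the article expects, so it marks an upper range.

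**Step 4. Which visits enter.** If only baseline and 6 months were entered, no observed 6-month score would be discarded. Neither Data Analysis nor Sample Size restricts the ANOVA in that way. Data Analysis speaks of between-group differences from baseline at follow-up, without naming visits.

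**The case against.** The strongest reply has three parts.

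**The conflict is inferred.** The article never says that incomplete patients are excluded or that all four time points go into one model. Imputation before the ANOVA would reconcile it with intention to treat, and a full protocol or SAP, not shown, may specify it. This stands. A reader might infer that the ANOVA and intention to treat cannot both hold; the documents do not support that. What remains is that the method named in two sections does not, as named, use all randomised patients, and would have to be changed or supplemented to do so.

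**Intention to treat may only mean analysed as allocated.** On that reading there is no breach of the label. Observed primary scores could still be discarded, and completers are still not the randomised groups.

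**Large numerical consequences are not established.** This also stands for three figures that a reader might reach:

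- *Power of about 76%.* 82 × 0.7 = 57.4 per arm gives about 76% at the assumed SD of 8. The shortfall below 63 arises because 246 is 189 × 1.3, whereas 189 / 0.7 = 270. That is a separate issue: with 90 per arm, a 30% loss would leave 63 and the planned power even with completers only.
- *Only 28 per arm.* 82 × 0.7³ = 28 requires 30% independent non-return at every follow-up. The article expects 30% loss overall and plans telephone reminders.
- *A stated bias in ODI points.* Losing the worst 30% at 3 months from one arm only, under one chosen set of correlations and SD 8, shifts the 6-month change contrast by about 0.8 points. Under equal correlations the shift is about 0. A figure near 2.0 belongs to a baseline-adjusted completers contrast, which the article does not plan.

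**Conclusion.** The point holds in a limited form. The named primary method deletes any patient with a missing score at a visit entered in the model, unless data are imputed first. With four ODI time points, postal follow-up and 30% expected loss, running it as named on all visits would make the primary result a completers analysis. Unless all loss is permanent and early, it would also throw away observed 6-month scores. This sits badly with the intention-to-treat statement, though it is not a proven contradiction.

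The size is a range. Under the loss patterns shown, between 0 and about 71 observed 6-month scores would be discarded, with 42 (221 against 179) in the illustration closest to the expected overall loss. This rests on all visits being entered, no imputation and assumed loss patterns. The direction and size of any bias cannot be derived from the document. The finding concerns the method that the article fixes; it does not fault the absence of a missing-data section.

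**What to change.** Amend Data Analysis, and the matching phrase in Sample Size, so that the primary analysis of ODI is a likelihood-based linear mixed model for repeated measures:

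- visit as a categorical factor, group × visit interaction, unstructured covariance;
- every available score of every randomised patient, in the allocated group;
- the group contrasts at 6 months as the primary estimate;
- the missing-at-random assumption stated, with a sensitivity analysis for departures from it;
- the complete-case ANOVA kept as a further sensitivity analysis, if wanted.

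Multiple imputation followed by the named ANOVA would also resolve the tension, but the mixed model does so directly and targets the 6-month contrast.

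Cost: a change of wording and a little more analysis work in standard software, with no new data, visits or patients. It should be settled before the statistician is unblinded. The recruitment inflation (189 × 1.3 against 189 / 0.7) needs its own correction; this change does not address it.

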For the researchers designing such walking programmes, and the clinicians delivering them, the challenge is to devise an effective intervention that will motivate habitually sedentary people with LBP to be physically active. A Cochrane systematic review of interventions to promote physical activity concluded that a mixture of self-direction and on-going professional support can encourage adults to be more physically active [28]. A randomised controlled trial found that an eight-week low frequency progressive walking programme for 'normal' sedentary adults had high levels of adherence, and resulted in increased physical activity levels with no adverse effects or injuries, thus increasing its clinical application [29]. Another trial reported evidence for the benefit to fitness and cardiovascular risk of the '30 minute brisk walking, five days per week' message to people aged 50–65 years who participated in a 12 week unsupervised home-based walking programme that used pedometers as motivational tools [30]. Pedometers are simple to use, inexpensive devices that produce a user-friendly output (step count, duration) that serves as an effective motivator to increase physical activity [31].

A self-activation programme by walking may be a more pragmatic and less costly intervention than supervised exercise classes to promote increased physical activity levels in patients with CLBP. It has the additional advantages of supporting a larger population of CLBP patients at the same time, and by moving the emphasis away from the hospital setting could reduce the costs to the Health Service. Given that the majority of patients with CLBP currently receive a range of interventions within the scope of 'usual' physiotherapy (advice, passive mobilization/manipulation, general exercise [32-34], this RCT will establish the difference in effectiveness of a walking programme and a supervised general exercise programme compared to usual physiotherapy, which will act as the control intervention, in subjects with chronic low back pain.

The *primary objective *is to:

(i) determine the difference between groups in mean change in functional disability at 6 months

The *secondary objectives *are to:

(ii) determine the difference between groups in mean changes in pain, health-related quality of life, psychosocial beliefs, days of sick leave, daily physical activity levels, self efficacy, readiness to change and patient satisfaction

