### Randomisation

Patients who have consented to participate will be randomly allocated in accordance with recognised procedures, by computer-generated random allocation sequences that will be prepared centrally by the trial statistician. This sequence will be used to randomly allocate each consenting, numbered subject to one of three study groups: supervised exercise class, walking programme or usual physiotherapy.

Stratification will be by hospital only and separate randomisation lists will be used for each hospital. Prior to randomisation each subject's group allocation preference will be sought and recorded by the Trial Co-ordinator in order to investigate whether treatment preference has any influence on outcomes.

The Trial Co-ordinator will telephone/text the Research Administrator who will provide a central, remote, telephone randomisation service, to obtain each consecutive subject's random group allocation. Following the baseline assessment an appointment for the relevant intervention will then be made by the Trial Co-ordinator. Each participant will receive a copy of 'The Back Book'[38] and be advised to read it before the first physiotherapy appointment. Participants allocated to the WP will be given an educational walking manual, and a Yamax Digiwalker Pedometer, instructed in its use and requested to wear it for seven days to record number of steps and habitual daily activity levels (frequency of walks, walk duration) in an exercise diary prior to the start of the intervention.

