#### Assessors

A blinded researcher will administer all outcome measures for postal follow-up. The Trial Co-ordinator will not be involved in follow-up outcome assessment. The statistician will be unaware of group allocation until completion of data analyses.

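### The primary method may change after the outcome data are inspected, on an unstated normality criterion, to an unnamed test that need not estimate the mean ODI change on which the objective and sample size rest

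*Protocol article*

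**What the plan says.** The primary objective, at the end of the Background, is to "determine the difference between groups in mean change in functional disability at 6 months". The Sample Size section says "A total of 189 patients (n = 63 per group) will be required for 80% power" to detect 4 ODI points, using a two-tailed repeated measures ANOVA that compares group means.

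The quantitative Data Analysis section makes that method conditional: "Continuous outcome variables will be analysed using a mixed between-within repeated measures analysis of variance if the assumptions for parametric statistics hold". The next sentence gives the alternative: "If substantial evidence of non-normality is found appropriate alternative (non-parametric) tests will be applied, and specified as the primary analysis method".

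On the statistician's role, the Randomisation section has allocation made "by computer-generated random allocation sequences that will be prepared centrally by the trial statistician". Under Blinding (Assessors) the article says "The statistician will be unaware of group allocation until completion of data analyses". Data Analysis adds: "Analysis of the clinical outcome data will be performed by the statistician who will remain blinded to group identification until analysis is complete". It also says that group allocation will be coded.

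**The concern.** The article does not merely leave the fallback undescribed. It states a rule under which the identity of the primary analysis is settled only after the outcome data have been examined. It does not say what counts as substantial evidence, whether raw scores, change scores or residuals are checked, or which test takes over.

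Two things are at stake. The first is the target. A rank test compares distributions through their ordering and does not yield a difference in mean change in ODI points, so the primary result might not answer the primary objective. The second is power. The trial was sized for a comparison of means, and that calculation does not carry over to an unnamed alternative.

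The natural safeguard for a choice made on the data is a blinded analyst. The article claims this, but it also has the trial statistician prepare the allocation lists, so the safeguard needs clearer wording.

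**Working it through.** **1. The plan's own sample size.** The inputs are a 4-point difference, two-sided 5%, 80% power and 63 per group (Sample Size). No SD is given, so 63 can only be back-solved. With the two-group formula for means:

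SD = 4 × √(63/2) / (1.960 + 0.842) = 8.01.

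Forward, an assumed SD of 8 gives n = 63 per group; SD 7 gives 49, SD 9 gives 80 and SD 10 gives 99. The figure is thus consistent with a comparison of means at an SD near 8. Applying the anticipated 30% loss to the 82 recruited per group leaves 82 × 0.70 = 57.4, about 57 per arm.

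**2. How often the switch would fire.** The article gives neither trigger nor variable, so both are assumed: Shapiro-Wilk at 5% on pooled within-arm residuals, 57 per arm, and beta-distributed scores on 0–100 with no difference between arms.

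| Variable checked | Assumptions | Normality rejected |
|---|---|---|
| Raw score | mean 35, SD 15 | 64% |
| Raw score | mean 30, SD 15 | 94% |
| Raw score | mean 25, SD 15 | about 100% |
| Raw score | mean 20, SD 13 | about 100% |
| Change score | baseline mean 30–35, follow-up mean 20–35, correlation 0.5 or 0.7 | about 5–15% |

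Repeat runs put the raw-score range at 62–100%. A looser trigger, absolute skewness above 1, is met in about 0–3% of trials on raw scores with mean 25–35 and about 20% with mean 20. The probability of changing the primary method therefore runs from almost nil to almost certain, depending on choices the article does not make.

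**3. Type I error when all arms share one distribution.** The ordinary F test on the raw beta scores rejects in 4.6–4.8% of null trials, so non-normality of this kind does not invalidate the mean comparison. The full two-stage rule (check, then one-way ANOVA or Kruskal-Wallis) was simulated with 63 per arm and 3,000 runs, on normal data and on gamma data with skewness 0.5, 0.75 and 1.0. It rejected in 4.6–5.1%. The same rule on the beta scores with 57 per arm gave 3.7–6.2%. There is no general inflation.

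**4. When arms differ in shape.** Illustration with 63 per arm and 3,000 runs. Two arms are normal with mean 0 and SD 8. The third is a mixture: 20% strong responders centred at 16 and 80% centred at −4, each with SD 6. Its mean is 0.2 × 16 − 0.8 × 4 = 0. In the second row of the table this arm is shifted by 4 points.

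| True mean difference | Switch fires | ANOVA rejects | Kruskal-Wallis rejects | Two-stage rule rejects |
|---|---|---|---|---|
| 0 | 50.5% | 4.7% | 10.0% | 8.4% |
| 4 points | 51.3% | 76% | 47% | 60% |

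In the first row Kruskal-Wallis is not malfunctioning: the distributions do differ. It answers a question other than the stated objective. In the second row, the mean difference for which the trial was sized is detected less often under the switch than under the planned ANOVA.

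**5. The statistician's role.** Set side by side, Randomisation has the list prepared by the trial statistician, while Blinding and Data Analysis have the statistician analyse while unaware of allocation. Only one statistician role appears. The Research Administrator gives out allocations by telephone. The article does not say who holds the key to the group codes.

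**The case against.** The strongest reply has four parts.

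First, the objective, the outcome definition and the Data Analysis section all speak of change from baseline. On change scores a 5% Shapiro-Wilk check fires only about 5–15% of the time under the assumptions above. A reader might infer that a bounded ODI would usually trigger the switch. That holds for raw scores under a 5% test, but the article names neither, and its word *substantial* could mean something much stricter. This part stands, and the firing rate is given here as a range.

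Second, the article says non-parametric, not rank. A permutation or bootstrap comparison of means would qualify and would keep the objective. This stands as a limit: the primary result can lose its target, but need not.

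Third, no loss of validity is shown when arms share a distribution, and the fallback's details may sit in a fuller plan. The first half stands. The second does not meet the point, because the published rule itself makes the primary method contingent on the data. A later plan could cure this only by replacing or tightly fixing that rule.

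Fourth, a reader might infer that the analyst could see which method favours which arm and choose accordingly. The documents do not support that. That the list's author and the analyst are one person is the natural reading but is not stated, and the article provides for coded groups and a blinded analysis. What remains is a tension in the wording.

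**Conclusion.** The point holds in limited form. The protocol article allows the primary analysis to be replaced after the data are inspected, without a criterion, a variable or a named alternative. If the alternative is a rank test, this conflicts with the mean-change objective and the basis of the sample size.

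The probability of switching cannot be determined from the document. The range of about 5–15% (change scores) to 62–100% (raw scores) rests on assumed beta distributions, 57 per arm and a 5% Shapiro-Wilk check. The fall in power from 76% to 60% rests on one assumed shape difference and shows direction, not an expected size. The rule should not be described as generally inflating type I error.

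The statistician's role is a secondary ambiguity to be cleared up, not evidence of a biased choice of method.

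**What to change.** Delete the sentence that promotes non-parametric tests to primary. State instead that the model for mean ODI is the primary analysis whatever the distribution, with robust or bootstrap confidence intervals for the between-group differences at 6 months. Any non-parametric analysis should be reported as a labelled sensitivity analysis and should not replace the primary result.

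Reconcile Randomisation with Blinding and Data Analysis. Either say that the person who prepares the sequences does not analyse the data, or say that the Research Administrator alone holds the key to the arm codes until the analysis is complete.

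The cost is analysis wording and one sentence on roles. Sample size, data collection and patient procedures do not change.

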### Cost Outcomes

Two cost outcomes will be used

(i) *Participants resource utilization *will be assessed using cost diaries developed and successfully used by the Principal Investigator in a previous RCT [54]. A random sample of 20% of cost diaries in each group will be verified by telephone interview with a researcher not involved in the day to day running of the trial to check the accuracy and ensure the quality of the data.

(ii) *Participant's health state *will be assessed using the EuroQol (EQ-5D) Questionnaire's Weighted Health Index [45] and Visual Analogue Scale.

Follow-up reminders will be given by phone and completed questionnaires returned by pre-paid envelopes.

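### The economic plan admits median ODI change as an effect unit and the VAS as a source of utilities; neither estimates what the analysis is meant to deliver

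*Protocol article*

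**What the plan says.** The economic question is secondary objective (iii) in the Background, and costs are also named in null hypothesis (a) under Hypotheses Tested. Data Analysis then fixes two choices.

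- **Cost-effectiveness.** "An additional cost effectiveness analysis will use the magnitude of a mean and median change on the Oswestry Disability Questionnaire", as the natural unit. Mean and median stand side by side, and neither is said to govern.
- **Cost utility.** "The resulting scores from the EQ-5D health state and the visual analog scale will be used to generate the health state utility values" needed for that analysis. Cost Outcomes makes the same pairing when it lists the EQ-5D "Weighted Health Index [45] and Visual Analogue Scale" as the measure of health state.

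Data Analysis also plans "mean and median health care utilization rates and associated direct service costs", together with patient costs. It adds that the cost utility analysis is meant to let the trial be set against other studies.

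**The concern.** An incremental cost-effectiveness ratio has a fixed meaning: the extra cost of treating a group divided by the extra effect gained by that group. Only arithmetic means carry that meaning, because a mean multiplied by the number treated gives the total. A median does not.

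A utility for a cost utility analysis likewise has a fixed meaning: a preference weight attached to a described health state. The VAS is the patient's direct rating of his or her own health. Dividing it by 100 changes the units but does not turn it into a preference weight.

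At stake is the answer to objective (iii). A median-based result could be read as cost per ODI point gained, and a VAS-based result as cost per QALY. Neither would be that, and the second would not be comparable with studies that use the weighted index.

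**Working it through.** **Inputs.** The document gives no cost, cost-effectiveness ratio, expected utility gain or distribution of ODI change, so there is no stated figure to reproduce. What can be checked is what the two stated rules would estimate. All numbers below are assumptions chosen for illustration.

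**Step 1: the target quantity.** For arms A and B,

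ICER = (mean cost A − mean cost B) / (mean effect A − mean effect B).

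Multiplying numerator and denominator by the number treated gives total extra cost over total extra effect, so the ratio describes the treated group. Replacing mean effect by median effect breaks this link, because number treated × median is not the total effect unless the distribution has equal mean and median.

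**Step 2: mean versus median ODI change.** Suppose that in arm A a fraction f of patients responds, with ODI improvement distributed N(20, SD 6), and the rest improve by N(2, SD 6). Let arm B be symmetric, with SD 8 and a mean 2 points below that of A. Then:

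- mean A = 20f + 2(1 − f)
- mean B = median B = mean A − 2
- median A is the m that solves f·Φ((m − 20)/6) + (1 − f)·Φ((m − 2)/6) = 0.5

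| f | Mean A | Mean = median B | Median A | Mean difference | Median difference |
|---|---|---|---|---|---|
| 0.30 | 7.4 | 5.4 | 5.34 | 2.0 | −0.06 |
| 0.40 | 9.2 | 7.2 | 7.51 | 2.0 | 0.31 |
| 0.45 | 10.1 | 8.1 | 9.08 | 2.0 | 0.98 |

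With an assumed extra mean cost of 100 in arm A, the mean-based ratio is 100/2.0 = 50 per ODI point in every row. With the median difference as denominator it is 100/0.98 = 102 for f = 0.45 and 100/0.312 = 321 for f = 0.40. For f = 0.30 the denominator is slightly negative, so arm A would look costlier and no better. If ODI change were symmetric in both arms, mean and median differences would agree apart from sampling error. The discrepancy therefore depends on shape, which the document does not give.

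**Step 3: index versus VAS.** Over one year, QALY gain = average utility difference × 1, and cost per QALY = extra cost / QALY gain. With the same assumed extra cost of 100:

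- gain 0.02: 100/0.02 = 5000
- gain 0.03: 100/0.03 = 3333
- gain 0.05: 100/0.05 = 2000
- gain 0.08: 100/0.08 = 1250

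If the index and the VAS gave different gains within this range, the cost per QALY would differ by up to 5000/1250 = 4-fold. The document does not say how far the two would differ, or in which direction.

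**Step 4: the two readings of the utility sentence.** It may mean two sets of utilities or one set built from both scores. Under the first reading, one of two cost utility results rests on something that is not a utility. Under the second, the only result mixes a preference weight with a self-rating. Both readings have the same defect.

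**The case against.** The strongest reply is that this is a condensed article. Naming a base case and an uncertainty method is commonly left to an analysis plan, so their absence here is not an error. That stands. The point rests on what the article does state: it names the median as an effect unit and the VAS as a source of utilities.

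Four stronger readings are tempting, and the document does not support them.

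- **Median costs enter the ratio.** The sentence on costs says only that means and medians will be calculated. That is ordinary description of skewed data, and nothing divides a median cost by an effect or adds medians across components. Illustrations built on skewed costs therefore do not bear on this point.
- **Four rival answers.** Cost per ODI point and cost per QALY are separate analyses. Mean or median affects only the first, and index or VAS only the second, so at most there are two versions of each.
- **The choice will be made after the data are seen.** The text does not say so.
- **Comparison with other studies is lost.** The weighted index is also collected, so an index-based analysis remains possible. The VAS version weakens that purpose but does not defeat it.

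It is also fair to say that the ODI divergence above needs an asymmetric response in at least one arm, and that the utility figures show sensitivity rather than an expected difference.

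**Conclusion.** The concern holds for the two stated rules. A cost-effectiveness analysis that uses median ODI change, and a cost utility analysis that uses VAS-derived or mixed utilities, would not estimate incremental effect per patient or QALYs in the intended sense.

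The size cannot be computed from the document. Under the assumed distributions, a true mean difference of 2.0 ODI points goes with a median difference of about −0.06 to 0.98, and the cost per QALY moves in inverse proportion to the assumed utility gain. These are illustrations, not forecasts.

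The reach is limited. A secondary objective is affected, with costs also named in null hypothesis (a). The primary comparison of ODI change at 6 months does not depend on either rule. The wording should be corrected, but nothing in the trial's design or data collection is at fault.

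**What to change.** In Data Analysis of the protocol article:

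1. Base the cost-effectiveness analysis on the difference in arithmetic mean cost and the difference in arithmetic mean ODI change, with an uncertainty method suited to skewed data, such as the bootstrap. Remove the median from the sentence that defines the effect unit, and keep medians of cost, utilisation and ODI change as description only.
2. Derive base-case utilities and QALYs from the EQ-5D weighted index only. Report the VAS separately as a health-status score or, at most, as a sensitivity analysis labelled as such.
3. Word the health-state entry under Cost Outcomes to match, so that the index is the source of utilities and the VAS is a separate score.

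The cost is a few changed words and a little more analysis work. No new data are needed, since the cost diaries, the ODI and both parts of the EQ-5D are already planned.
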